### Study Population

Recruitment is predominantly conducted online to reflect the online nature of the DA. We make use of various methods: Mainly, we are recruiting participants through project social media accounts (eg, [28]) and paid social media advertisements. We decided to make use of 4 big social media platforms (ie, Facebook, Instagram, Twitter, and LinkedIn) as they cater to different target groups [29]. In addition, our recruitment messages are being shared on the social media accounts of the project members and their institutions. Also, we promote the RCT through the project’s website, and we asked various relevant Dutch institutes and organizations (eg, the Dutch institute for addiction and mental health and municipal health services) to promote the study. Finally, we advertise the study in online newspapers. All recruitment materials include a link to enroll in the RCT, if possible, to simplify the process for potential participants as much as possible. Study inclusion criteria are: (1) participants are currently smoking, (2) participants are motivated to stop smoking within 6 months, (3) participants are 18–100 years old, (4) participants are able to understand Dutch, and (5) participants have access to the internet and have the necessary internet literacy skills to use the intervention. People are excluded if they only use e-cigarettes; however, dual users can participate. The rationale behind the inclusion and exclusion criteria is described in Table 1.

**Table 1 table1:** Overview of the randomized controlled trial inclusion and exclusion criteria, including rationale.

Criteria			Rationale
**Inclusion criteria**			
	Participants are currently smoking	To test the primary hypothesis that the DA will have a positive effect on smoking cessation, it has to be tested among smokers	
	Participants are motivated to stop smoking within 6 months	As smokers unmotivated to quit cannot be expected to be willing to consider the use of cessation assistance	
	Participants are 18–100 years old	As the DA was developed for adults	
	Participants are able to understand Dutch	To ensure that participants understand all provided information	
	Participants have access to the internet and have the necessary internet literacy (skills) to use the intervention	As the DA is fully online, participants need both access to the internet and the necessary internet literacy (skills) to access and use the DA	
**Exclusion criteria**			
	Participants exclusively use e-cigarettes	As there is no consensus on whether cessation assistance tools can be used to cease e-cigarette use	

### Required Sample Size

The power calculation was based on the dichotomous outcome measure of smoking abstinence (primary outcome: 7-day point prevalence abstinence). The only previous RCT in the Netherlands testing the effect of a DA for smoking cessation on this outcome measure showed a significant effect (20.2% vs 13.6%) at 6 months [14]. To be able to significantly (α=.05; β=.20) detect the same effect in a 1-sided test, 398 smokers per arm are necessary at the end of the trial (796 in total). Considering 50% attrition over the intervention period, we aim to include 1592 smokers at baseline.

### The Intervention

#### Initial DA Development

The development process of the DA was based on the IPDAS guidelines for DA development [30]. In line with these guidelines, both end users’ (ie, smokers) and clinicians’ needs were assessed. In addition, we asked scientific smoking cessation experts for extra input as smoking cessation is often done without consulting clinicians — especially in the Netherlands [8]. In the end user needs assessment, 20 interviews were conducted to assess end users’ needs regarding potential cessation assistance’s characteristics that should be described in the DA and DA functions (eg, a knowledge quiz). The input of the experts was gathered through 2 Delphi studies (24 scientists and 38 clinicians completed the final round). The input of these 3 qualitative studies was used to inform the design and content of the DA, supplemented by the IPDAS background papers (eg, [31]) as well as other relevant literature in the field (eg, [23]) and in consultation with established experts in the field. The SDT served as the theoretical framework. After this, a first prototype was developed that was alpha-tested in September 2019 with potential end users (n=3) and Dutch smoking cessation experts (n=8). During the alpha test, participants were asked to focus on the content of the DA. The end users alpha-tested parts of the DA, while the smoking cessation experts tested the whole first version. Before the beta test, the DA was evaluated by 1 of the co-authors (JR) with regard to the comprehensibility of the text for people with limited health literacy. On the basis of that evaluation, some sections and sentences were rephrased or simplified.

#### Usability Testing

In December 2019, after the alpha test, the DA was beta-tested among 15 experts and end users: 5 smoking cessation counselors, 5 eHealth experts (of whom, 2 had digital DA experience), and 5 potential end users (ie, people motivated to stop smoking). Respondents were given access to the DA to assess the DA’s usability using the heuristic evaluation method (smoking cessation counselors and eHealth experts) and the think-aloud method (potential end users) [32].

Using the heuristic evaluation method, smoking cessation counselors and eHealth experts were asked to evaluate the DA against a list of recognized usability principles: (1) use simple and natural dialogue, (2) speak the user’s language, (3) minimize memory load, (4) be consistent, (5) provide feedback, (6) provide clearly marked exits, (7) provide shortcuts, (8) provide good error messages, (9) prevent errors, and (10) provide help and documentation.
The smoking cessation counselors and eHealth experts were asked to use predetermined scenarios (eg, whether cessation attempts have been undertaken before) during the evaluation.

With the think-aloud method, end users were asked to complete the DA while verbalizing their thoughts. The think-aloud method is considered particularly useful in understanding processes of cognition and is considered to be of high value in evaluating an intervention’s design on usability flaws [32].

Data gathered through these tests were compared and compiled into a summary describing the usability flaws of the DA. Based on these results, adjustments to the DA were identified, which can be seen in Textbox 1.

Overview of alterations to the decision aid (DA).More information was added on how to use the DA: for example, “Now click on 'next' to start with the information.”The language and complexity level have been simplified.Certain subparts (eg, results of the knowledge quiz) were rewritten in a more positive tone.Content was shortened if possible (eg, by combining pages or by removing too many details).Some content was added (eg, required duration of prescription medication use).More visuals were added (eg, icon arrays to showcase cessation assistance’s effectiveness).Information regarding cessation assistance’s effectiveness was adapted to make it more accessible.The order of the given information was changed (eg, information regarding non-evidence–based cessation assistance was moved to the beginning as testers found it confusing that this information was mentioned only at the end of the information section).A function was added to enlarge visuals and tables.The layout was changed to make the DA more accessible to users with visual impairments (eg, we added more lines and changed the color of the text).All abbreviations were removed, as were references to terms that were used in other parts of the DA.All hyperlinks were removed.Two possible options (ie, combination of behavioral support and nicotine replacement therapy; combination of behavioral support and prescription medication) were added.A ranking of the evidence-based cessation assistance tools based on the value clarification method was added.

#### Description of the DA

An interactive Dutch DA with an explicit VCM and tailored advice that facilitates the process of choosing an evidence-based cessation assistance was developed. The DA follows a stepwise approach and is designed to encourage a decision that is autonomous and consistent with participant’s values and smoking behavior. The DA consists of 8 sequential sections: (1) information section, (2) optional knowledge quiz, (3) brief smoking assessment, (4) intuitive decision, (5) intermediate advice, (6) explicit VCM, (7) tailored advice, and (8) access information.

In step 1, the information section explains the decision at hand, as well as all the available cessation assistance in the Netherlands. The following topics are addressed: (1) smoking cessation with and without evidence-based cessation assistance, (2) non-evidence–based cessation assistance, and (3) evidence-based cessation assistance.

For the first topic, differences in smoking cessation outcomes are described between people using and not using evidence-based cessation assistance using simple frequency formats (eg, “By using one or more of these stop methods, 15 out of 100 people are still smoke-free after one year.”).

For the second topic, a list of various non-evidence–based cessation assistance tools (ie, acupuncture, laser therapy, hypnotherapy, mindfulness, smartphone apps, self-help books, and e-cigarettes) are described, and a remark is made that the use of these tools is not advised.

For the third topic, evidence-based cessation assistance is described (Table 2), including behavioral support in general, in which users can choose to read more detailed information about all possible options (ie, face-to-face counseling, counseling over the phone, group coaching, and eHealth); NRT in general, in which users can choose to read more detailed information about all possible options (ie, nicotine patches, nicotine gum, nicotine lozenge, nicotine mouth spray, and nicotine inhaler); prescription medication in general, in which users can choose to read more detailed information about all possible options (ie, varenicline, bupropion, and nortriptyline); and cessation assistance during pregnancy and breastfeeding. Users can compare all cessation assistance options using an option grid and are informed about combinations of multiple cessation assistance options. In addition, costs and reimbursement are described, and sources used to inform the information section content (ie, reports, scientific manuscripts, websites) are provided.

**Table 2 table2:** Overview of cessation assistance characteristics included in the decision aid (DA).

Cessation assistance characteristic	Rationale for inclusion in the DA	This characteristic is included in the statements (VCM^a^) for:
Effectiveness of the cessation assistance options	During the interviews with potential end users, this was both the most mentioned characteristic and considered the most important characteristic.	Behavioral support, prescription medication
Probability of nausea and dizziness when the cessation assistance option is used	Probability of side effects was the third most often mentioned characteristic during the interviews with potential end users and was also considered to be of importance by the clinicians. The first 3 side effects were specifically named as important by potential end users, while the fourth was added, as this is a common side effect. Other side effects were included if they are regarded as being very likely to occur.	Nicotine replacement therapy, prescription medication
Probability of mood changes when the cessation assistance option is used		
Probability of headaches when the cessation assistance option is used		
Probability of sleeping problems when the cessation assistance option is used		
Probability of other side effects that are very likely to occur when the cessation assistance option is used		
Extent and type of contact someone has with a professional when the cessation assistance option is used	Both scientists and potential end users indicated that this was of great importance. Clinicians indicated that required contact with a health care professional was of great importance.	Behavioral support
How the cessation assistance option is used	This was integrated after it had been decided that Dutch health insurance companies would cover evidence-based cessation assistance use, as that left too few features to distinguish between the different nicotine replacement therapies and prescription medication.	Nicotine replacement therapy, prescription medication

^a^VCM: value clarification method.

In step 2, users can choose to complete the knowledge quiz or skip the knowledge quiz and proceed to the following step. If they complete the knowledge quiz, they will receive the results, see the correct answers to the questions that they answered incorrectly or could not answer (seeing the correct answers can also be skipped even if a respondent opts to do the knowledge quiz), and proceed to the following step.

The brief smoking assessment in step 3 consists of 2 closed (yes/no) questions: “To ensure that our advice suits you best, we would like to ask you if you smoke more than 10 cigarettes (or other tobacco products) on a normal day?” and “To ensure that our advice suits you best, we would like to ask you if you have ever made one or more smoking cessation attempts in the past that were unsuccessful?”

In step 4, an intuitive decision occurs between different clusters of cessation assistance tools: behavioral support; NRT; combination of behavioral support, NRT, and prescription medication; combination of behavioral support and NRT; combination of behavioral support and prescription medication; other, non-evidence–based cessation assistance; and no cessation assistance at all.

In step 5, intermediate advice is provided for users to reevaluate their intuitive decision in step 4 when they chose behavioral support only or NRT only, while also affirming at least 1 of the 2 questions in step 3 (indicating that they smoke more than 10 cigarettes on a normal day or have made one or more smoking cessation attempts in the past): They are advised to consider using a combination of behavioral and pharmacological cessation assistance tools. Intermediate advice is also given to users who chose non-evidence–based cessation assistance or no cessation assistance at all regardless of their answers in step 3: They are advised to consider using one or more evidence-based cessation assistance tools.

The explicit VCM in step 6 is provided for users that chose evidence-based cessation assistance tools in steps 4 or 5; users are asked to rate certain statements regarding cessation assistance characteristics (eg, “I prefer a stop method that works better, even if that means that I have to leave the house.”). These statements are also described in Table 2. Users only rate statements for options that belong to the cluster of cessation assistance options they selected in the previous step.

Step 7 is tailored advice based on the explicit VCM and an optional ranking of all options. The advice is given only when it is possible to give clear advice (ie, if users’ scores do not suggest that more than 2 cessation assistance tools are suitable based on their indicated values).

Step 8 involves accessing information on how to obtain the chosen cessation assistance (eg, nicotine patches).

Above and beyond these 8 steps, framing throughout the DA is positive and autonomy-supportive [33] (in line with the SDT as theoretical framework) to support users’ need for autonomy (eg, we refrained from using fear appeals [34] and controlling language [12,33]). We also clearly communicate that users can make their own choice at the end and included “cues” to support this process (again in order to support users’ need for autonomy; eg, by stating that the advice is only a recommendation and not a command and that it might be a good idea to discuss this with either the social environment, a health care provider, or both). A flow chart of the DA can be seen in Figure 1. The digital DA is hosted by the Dutch company OverNite Software Europe BV, and we make use of their product “TailorBuilder” [35]. Translated screenshots of different sections can be seen in Figure 2 (example of the information section) and Figure 3 (example of the explicit VCM).

**Figure 1 figure1:**
[figure not shown]
Sections of the decision aid. VCM: value clarification method.

**Figure 2 figure2:**
[figure not shown]
Screenshot of the information section in the decision aid (original text translated from Dutch).

**Figure 3 figure3:**
[figure not shown]
Screenshot of the value clarification method (VCM) in the decision aid (original text translated from Dutch).

#### Theoretical Background of the Different Sections

An information section was predominantly included as relevant knowledge is needed to engage in high-quality decision making [36] and as it is regarded as an active ingredient by the IPDAS [37,38]. Given this fact, and as potential end users indicated that they would like a knowledge quiz within the DA, a knowledge quiz was included at the end of the information section. Users are thus able to check for themselves if they have the necessary knowledge to engage in the decision process and can obtain additional information if desired. The content of the information section was mainly based on Dutch guidelines (eg, [39]), supplemented by various Cochrane reviews (eg, [40]), online information from the Dutch National Health Care Institute [41], and the Dutch Medicines Evaluation Board [42].

An intuitive decision to limit the choice set for the explicit VCM was included to both prevent choice overload [43] and to include intuitive decision-making processes in the DA. Choice overload describes a scenario in which the difficulty of the decision to be made is greater than the cognitive means of the person faced with the decision, due to too many options. Many DAs focus on a rather small set of available options [44] (eg, deciding between intensive or less intensive aftercare after breast cancer treatment [45]); yet, a cessation assistance DA has to include more options to present all available possibilities. Considering that the comparison of too many characteristics of too many options can lead to choice overload, which can in turn lead to worse decisional outcomes [43], in step 4 of the DA we decided to have users intuitively choose to go on with a limited choice set (eg, only behavioral support). Another benefit of this approach is that users are encouraged to make use of both deliberative and intuitive decision-making processes. While many DAs focus on facilitating deliberation, de Vries et al [36] have argued that combining those 2 strategies can lead to improved decisional outcomes. Importantly, however, users receive information about all possible options before they intuitively make a first, broad decision as knowledge is regarded as a necessary prerequisite for high-quality intuitive decision making [36].

As the Dutch smoking cessation guideline indicates that a combination of both behavioral and pharmacological support should be considered if smokers smoke >10 cigarettes per day or if many of their past cessation attempts failed [39], users that indicated in step 3 that this applies to them are provided with information on the improved effectiveness of a behavioral and pharmacological combination. Of course, even then, they can autonomously decide to continue with another cessation assistance set — in line with their preference and the SDT. In case smokers choose to use either no cessation assistance or no evidence-based cessation assistance, they are also reminded that evidence-based cessation assistance will probably lead to more successful cessation outcomes, but if they choose not to change their mind, they are directed to the last step (ie, access information) if they decided to use no cessation assistance or directly to the end if they decided to use no evidence-based cessation assistance.

We decided to use an explicit VCM in the intervention group as VCMs are regarded as active ingredients by the IPDAS [20,37], and while conflicting evidence exists [46], an overwhelming amount of research has shown that interactive methods to clarify people’s values seem to result in better decisional outcomes [22], especially in the long run [21] and if people are supported in understanding the implications of their clarified values [23,24]. This is why we decided to integrate individual tailored advice that is supplemented with information on how to obtain the different cessation assistance options to remove barriers for the users.

### Study Comparator Group

Participants in the control group receive the same DA without an explicit VCM and tailored advice; thus, the DA includes the following steps: (1) information section, (2) optional knowledge quiz, (3) brief smoking assessment, (4) intuitive decision, (5) intermediate advice, and (8) access information. Steps 6 and 7 are skipped. The only other difference is that participants in the control group are not immediately directed towards the end after they have chosen to use no evidence-based cessation assistance to also provide them with a chance to reevaluate their choice. More information about the individual steps can be found under “Description of the DA.”

### Trial Flow and Measurement Instruments

As participants register for the study via an online form, which includes their provision of informed consent and the creation of an account, participants are automatically randomized into 1 of the 2 groups (intervention or control group), allocating approximately 50% of respondents to either group. After this, they are asked to fill in the first part of the baseline questionnaire (t=0) consisting of 22-94 items (depending on the respective answers; eg, if the participants state that they have never attempted to cease smoking, no follow-up questions are posed), in which general demographic information (eg, age), smoking behavior, nicotine dependence, productivity loss, health care utilization, quality of life, and stages of decision making are assessed. Participants are excluded from the study if they indicate that they are <18 years old, do not smoke, are not motivated to stop smoking within 6 months, or only use e-cigarettes. Participants immediately receive access to 1 of the 2 DAs after being randomized, as this process is fully automated. After having accessed the DA, the second part of the baseline questionnaire is made available (t=1). The second part consists of 53-56 items regarding stages of decision making, the decision, the decision-making process, knowledge, perceived autonomy support, perceived competence, user evaluation, and recruitment channels.

One month after the baseline questionnaire (t=2), users are asked to fill in a short follow-up questionnaire consisting of 14-21 items regarding cessation assistance utilization, smoking cessation status, stages of decision making, and knowledge.

After 6 months (t=3) and 12 months (t=4), users are asked to fill in a longer follow-up questionnaire that consists of 16-88 items relating to cessation assistance utilization, smoking abstinence (7-day point prevalence abstinence and prolonged abstinence), and questions regarding smoking behavior for those that did not achieve smoking abstinence. Health care utilization, productivity losses, quality of life, and decisional regret are also assessed (again). During t=4, 2 qualitative items are included to assess users’ experience of having used the DA during their cessation attempt.

All included measures are based on our theoretical background (ie, SDT [47,48]), the IPDAS guidelines on establishing effectiveness of DAs [49], Dutch guidelines on health economic evaluation [50], and expert knowledge regarding smoking cessation outcomes [51,52]. For a more detailed overview of all included constructs, measurements, and their respective sources, see Table 3.

**Table 3 table3:** Overview of included constructs, measurements, and sources.

Constructs		Measurements and sources	Purpose

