**Baseline (t=0): directly before the decision aid**			
	Demographics	Age, gender, education [52]	Sample description, attrition analyses, covariate(s) in (main) analyses
	Smoking behavior	Smoking status, motivation to quit, type of tobacco products, amount of tobacco consumption, amount of past cessation attempts, and cessation assistance utilization in the past 6 months [52]	Sample description, attrition analyses
	Nicotine dependence	Revised Fagerström Test for Nicotine Dependence (FTND-R) [53]	Sample description, attrition analyses, covariate in (main) analyses
	Productivity loss	iMTA Productivity Cost Questionnaire (iPCQ) [54]	Economic evaluation
	Health care utilization	Contacts with health care professionals (plus frequency) in the past 6 months, cessation assistance utilization (plus frequency) in the past 6 months [55]	Economic evaluation
	Quality of life	ICEpop CAPability measure for Adults (ICECAP-A) [56]	Economic evaluation
	Stages of decision making	Stage of Decision Making [57]	Sample description, attrition analyses, process information, covariate in (main) analyses

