## Results

The RCT started in January 2020, and at this writing, 1248 users created an account, of which 519 finished the DA. Data collection is ongoing and will be conducted until September 2021.

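### Randomisation at account creation precedes eligibility, t=0 and any difference between the arms, and follow-up is then limited to people who finished the DA

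*Protocol article*

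**What the plan says.** All references are to the protocol article.

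- **Allocation.** Under Trial Flow and Measurement Instruments, people sign up on a web page, "which includes their provision of informed consent and the creation of an account, participants are automatically randomized into 1 of the 2 groups".
- **Baseline questionnaire.** The text continues: "After this, they are asked to fill in the first part of the baseline questionnaire (t=0"). Table 3 lists "Smoking status, motivation to quit, type of tobacco products" among the t=0 items, under the label "Baseline (t=0): directly before the decision aid".
- **Exclusions.** "Participants are excluded from the study if they indicate that they are <18 years old, do not smoke", and the sentence goes on to smokers not motivated to stop and people who use only e-cigarettes.
- **Access.** "Participants immediately receive access to 1 of the 2 DAs after being randomized", with the explanation that the process is automated.
- **Difference between arms.** In the control DA, "Steps 6 and 7 are skipped" (Study Comparator Group). The same section names one other difference: controls who choose assistance that is not evidence-based are not sent straight to the end.
- **Follow-up.** The paragraph after Table 3 invites people to the follow-up questionnaires on condition that they went through the whole DA.
- **Progress.** At writing, "1248 users created an account, of which 519 finished the DA" (Results).
- **Target.** Required Sample Size asks for 398 per arm at the end of the trial and, with 50% attrition, 1592 smokers at baseline.

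**The concern.** Allocation comes earlier than anything that needs it. It precedes the answers that decide eligibility, the baseline measurements, and the steps in which the two DAs differ. Two groups are randomised as a result and can tell us nothing about the VCM and tailored advice: people found ineligible at t=0, and people who leave during t=0 or the common steps. They must either be removed after randomisation or be carried in an all-randomised analysis, where they dilute the contrast.

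The follow-up rule then decides in practice who has outcome data, and it does so at a worse place. Finishing the DA is observed after the arms have diverged, and the intervention arm has two more steps to get through. If those steps change who finishes, the people followed in the two arms are no longer comparable by design. This affects H1 to H3, which rest on the 1-, 6- and 12-month questionnaires.

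**Working it through.** **1. The plan's own sample size.** Inputs from Required Sample Size: 20.2% v 13.6%, one-sided α = 0.05, power 80%. With pooled variance and no continuity correction, n per arm = [z(α)·√(2·p̄·q̄) + z(β)·√(p1·q1 + p2·q2)]² / (p1 − p2)².

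- p̄ = 0.169, so √(2 × 0.169 × 0.831) = 0.530.
- √(0.202 × 0.798 + 0.136 × 0.864) = 0.528.
- (1.645 × 0.530 + 0.842 × 0.528)² / 0.066² = 397.6, rounded up to 398.
- 2 × 398 = 796, and 796 / 0.5 = 1592.

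Both figures reproduce. The timing of allocation does not alter the 398. It bears only on whom the 1592 counts.

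**2. Order of events.**

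| Event | Position | Can the arm affect it? |
|---|---|---|
| Consent, account, allocation | first | – |
| t=0 and eligibility answers | after allocation, before the DA | No: no difference met yet, and participants are described as blinded |
| Steps 1 to 4 | common to both arms | No |
| Step 5 and routing after it | common, but the routing rule may split near here | Not certain |
| Steps 6 and 7 | intervention only | Yes |
| Finishing the DA | after the split | Yes |
| Invitation to follow-up | only after finishing | Yes, through finishing |

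A set fixed at any row marked No keeps the randomised comparison. A set fixed by finishing does not.

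**3. Size of the group.** 1248 − 519 = 729, and 729 / 1248 = 58.4% of accounts had not finished; 519 / 1248 = 41.6% had. The 729 mix ineligible people, early leavers, people who left after the split and users still in progress. The article does not give the breakdown, nor the finishing rate by arm.

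**4. Dilution, as an illustration.** Suppose a share s of those randomised has the planned rates and everyone else is counted as smoking in both arms. The difference is then s × (20.2 − 13.6) = s × 6.6 percentage points. At s = 1 it is 6.6; at s = 0.416 it is 2.7 (8.4% v 5.7%). The true s is not known, because accounts include ineligible people who would be excluded and users not yet finished. The worst-case approach under Analysis of Primary and Secondary Outcomes treats dropouts as unchanged, but the article does not say whether that covers randomised people who never finished the DA.

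**The case against.** **The exclusions do no harm to validity.** This stands. The answers are given before the DA, by participants described as blinded, under automatic allocation. A reader might infer that excluding ineligible people after randomisation breaks the comparison; the documents do not support that. It is avoidable loss and untidy accounting.

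**The order is not contradictory.** Largely right. A reader might infer from "Participants immediately receive access to 1 of the 2 DAs after being randomized" that some people enter the DA before t=0. The sentence gives automation as its reason, so it most plausibly means no manual delay, and the rest of the section agrees with Table 3 on allocation, t=0, DA. The trial-flow figure is not available to us. What remains is loose wording.

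**A power loss can be calculated.** A reader might take 1592 × 0.416 = 662 finishers (331 per arm) and obtain one-sided power of 73%, or 48% if half are then lost. These figures hold only if the 1592 are registrations and the interim completion rate persists. The article speaks of smokers at baseline, whereas accounts include people later excluded as non-smokers. On the registration reading, non-completion may already be part of the 50% attrition, so the 48% could count it twice. Nor do the figures measure this defect: a given number of registrations yields about the same number of finishers wherever allocation occurs.

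**Moving allocation does not cure the selection.** Correct. Even with allocation after the last common step, inviting only finishers would still select across steps 6 to 8. The follow-up rule has to change as well.

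**Completion of step 5 is not a secure boundary.** Also correct. Step 5 advice goes only to some users, and the article does not show whether the routing difference begins before or after step 5 ends.

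**Conclusion.** The point holds as a design weakness worth correcting. Allocation at account creation puts ineligible people and early leavers into the randomised population for no gain, since the process is automated and the arms share steps 1 to 5 apart from the routing rule. By itself that costs clarity and, in an all-randomised analysis, dilution.

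The threat to validity is the follow-up rule, which conditions outcome data on behaviour observed after the arms diverge, with two more steps in one arm. Its direction and size cannot be judged without finishing rates by arm.

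The documented scale is 729 of 1248 accounts (58.4%) not finished at writing, an interim count of mixed composition. No power figure should be attached. The conclusion rests on the stated sequence, on both DAs being the same up to the routing split, and on blinding as described under Potential Strengths of the Study.

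**What to change.** 1. Move the automated allocation to after t=0 is submitted and eligibility confirmed. It may move further, to the last point common to both arms, once the sponsor confirms where the routing described under Study Comparator Group splits. If the split lies inside step 5, that point is the step 4 choice.
2. For people already randomised, define the primary analysis set as all eligible people who reached that common point, by assigned arm, whether or not they finished the DA. Report earlier losses and exclusions by arm.
3. Send the follow-up questionnaires to everyone in that set, in place of the condition that the whole DA was used. For people already past a time point, the later questionnaires can still be sent.
4. State from which point the 1592 is counted, and whether dropouts in the worst-case analysis include people in the set who did not finish.
5. Reword the sentence on immediate access so that the order reads t=0, allocation, DA.

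**Cost.** A software change during the trial, two enrolment periods with different allocation points to describe, and some extra automated invitations. The documents do not show whether the hosting platform can allocate part-way through the DA, so allocation directly after t=0 is the safer minimum. The required 398 per arm is unchanged. If the 1592 is counted from a later point than now intended, more registrations will be needed to reach it.
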